## Abstract

**Introduction:**

Permanent artificial pacemaker implantation is a safe and effective treatment for bradycardia and is associated with extended longevity and improved quality of life. However, the most common long-term complication of standard pacemaker therapy is pacemaker-associated heart failure. Pacemaker follow-up is potentially an opportunity to screen for heart failure to assess and optimise patient devices and medical therapy.

**Methods and analysis:**

The study is a multicentre, phase-3 randomised trial. The 1200 participants will be people who have a permanent pacemaker for bradycardia for at least 12 months, randomly assigned to undergo a transthoracic echocardiogram with their pacemaker check, thereby tailoring their management directed by left ventricular function or the pacemaker check alone, continuing with routine follow-up. The primary outcome measure is time to all-cause mortality or heart failure hospitalisation. Secondary outcomes include external validation of our risk stratification model to predict onset of heart failure and quality of life assessment.

**Ethics and Dissemination:**

The trial design and protocol have received national ethical approval (12/YH/0487). The results of this randomised trial will be published in international peer-reviewed journals, communicated to healthcare professionals and patient involvement groups and highlighted using social media campaigns.

**Trial registration number:**

NCT01819662.

Strengths and limitations of this studyOPTimising PACEmaker therapy is a trial independently funded by the National Institute for Health Research.Stratification of the participant randomisation is not adopted in this trial due to the large sample size.Participant and practitioner blinding are not plausible.The control arm consists of current standard of care ensuring trial results are reflective and generalizable.

## Introduction

Permanent artificial pacemaker implantation is a safe and effective treatment for bradycardia^1^ and is associated with extended longevity^2^ and improved quality of life.^3^ An estimated 350 000 people in the UK have a pacemaker, with over 40 000 new implants per year.

However, long-term right ventricular (RV) pacing has been linked to adverse left ventricular (LV) remodelling,^4 5^ such that the most common long-term complication of standard pacemaker therapy is pacemaker-associated chronic heart failure (CHF) due to left ventricular systolic dysfunction (LVSD).^6–8^ While up to 2%–3% of the general population have CHF, the condition is much more common in pacemaker patients with a prevalence up to 50%^7 9^ and 12% of people admitted with acute decompensated heart failure (HF) (4% with a de novo admission for HF) have a pacemaker.^10^

It is clear that RV pacing alone can lead to LVSD; however, the risk is especially high in people requiring a high proportion of ventricular pacing, those with diabetes mellitus, previous myocardial infarction and raised creatinine.^11^ Data examining the relationship between pacemaker use and cardiac dysfunction predominantly originate from retrospective cross-sectional analysis or secondary analyses.^12–15^ We provided the first evidence that reducing RV pacing through careful reprogramming is associated with an improvement in LV function without affecting quality of life or functional capacity,^9^ confirming somewhat the suggestion that RV pacing is contributory to LV dysfunction in pacemaker patients and not just a bystander in a multimorbid patient population.

Although there is increasing recognition of the axis of RV pacing and LVSD, it remains the case that HF is frequently overlooked in the pacemaker population with symptoms often ascribed to pacemaker syndrome, chronotropic incompetence or comorbidities.^6^ HF and undiagnosed LV dysfunction have a major effect on mortality and morbidity among pacemaker patients.^16–18^ Since HF management accounts for approximately 2% of the healthcare budget in many developed countries, more than 60% of which relates to hospitalisation costs,^19^ optimal management of people with HF whether or not they have a pacemaker is a key strategy for controlling healthcare costs while increasing quality of life.^20^

There are, however, no data on the potential benefits of screening people with pacemakers for HF, and while there are now a series of algorithms to limit RV pacing,^21–23^ no clear strategy for the use of these is outlined in current guidelines. This situation is compounded by a lack of published evidence around the benefits of medical management of pacemaker-related HF since people with pacemakers were excluded from most of the large HF studies.

Prospective randomised studies of pacemaker follow-up programmes to risk stratify patients and optimise management have not yet been of adequate size and duration to assess the clinical effectiveness of such an approach in a real-world general healthcare setting. Pacemaker follow-up is a rarely realised opportunity to screen for HF and assess and optimise patient devices and medical therapy.^24^

The OPTimising PACEmaker therapy (OPT-PACE) trial has been designed to address these issues and quantify time to all-cause mortality or HF hospitalisation, as well as validate a HF risk stratification model based on simple variables available in pacemaker clinic. Secondary aims are to establish whether N-terminal prohormone of brain natriuretic peptide (NT-proBNP) improves this risk stratification model. Subsequently, we aim to provide data on the effects of establishing the presence of LVSD on medical therapy, device programming and patient quality of life.

### Pilot data

#### Risk model

The design of the OPT-PACE trial is informed by an observational cohort^11^ including 491 patients listed for a pacemaker generator replacement in a single tertiary centre (Leeds Teaching Hospitals NHS Trust) invited for pacing therapy information, diagnostic pacing data and an echocardiogram.

Of this cohort, 40% had a left ventricular ejection fraction (LVEF) of <50%, which was much higher (59%) in those with >80% RV pacing (p<0.001), demonstrating that patients with RV pacemakers have a high prevalence of LVSD. After a mean follow-up time of 668 days, 56 patients (12%) had died or been hospitalised for HF.

Multivariable analyses identified a number of simple clinical variables; high percentage RV pacing, high serum creatinine and previous myocardial infarction as potential independent predictors of LVSD to identify patients who may benefit from a more comprehensive review.^11^ This risk model requires external validation planned within the OPT-PACE trial.

### Intervention development

The design of the pacemaker optimisation intervention used in the OPT-PACE trial is based on data from an observational cohort of 66 patients, referred for pacemaker generator replacement, recruited consecutively from a single tertiary centre (Leeds Teaching Hospitals NHS Trust).^9^ All patients recruited had been referred for pacemaker generator replacement. Exclusion criteria were inability to consent, underlying complete heart block, a life expectancy of <1 year in the opinion of the clinician (eg, terminal malignancy), the presence of a device-related complication or those with known LVEF <50%.

In patients recruited with avoidable RV pacing, a prespecified protocol was followed to reduce this as outlined in figure 1, including a reduction in the diurnal base rate (BR) to 50 beats/min with nocturnal rate or hysteresis to 40 beats/min along with the deactivation of rate-adaptive pacing. In addition, where sinus rhythm and heart block had been documented, the atrioventricular delays were extended or a device with RV avoidance algorithms was implanted. The patients were reassessed 6 months post randomisation. The primary endpoint was LVEF at follow-up calculated as an average over three non-paced, normally conducted beats using modified Simpson’s method as per American Society of Echocardiogrpahy guidelines.^25^ The protocol was tolerated in all but two subjects in whom rate-responsive pacing was reactivated. Nevertheless, application of the protocol reduced absolute RV pacing percentage by a mean of 49% (95% CI 41% to 57%; p<0.0001) from baseline and resulted in a mean absolute improvement in LVEF of 6% (95% CI 2% to 8%; p<0.0001). This occurred without reduction in exercise capacity, NT-proBNP or quality of life. An association was seen between the reduction in RV pacing and magnitude of change in LVEF (p=0.04). The intervention was considered safe to use without adaptation in OPT-PACE.

**Figure 1 F1:**
[figure not shown]
Ventricular pacing avoidance protocol.^9^

## Methods and analysis

OPT-PACE is a multicentre, randomised, non-blinded parallel trial funded by the National Institute for Health Research (NIHR) in the UK (NIHR-CS-2012-032) and registered with the Clinical Trials registry. The trial design and protocol have received approval from necessary regulatory and ethics boards as well as an independent trial steering committee.

The trial will recruit 1200 patients, which began in June 2013 and all patients will be followed up for a minimum of 12 months.

Trial participation may be terminated via voluntary refusal to continue at any time or through significant clinical deterioration assessed by medical staff. Participants suffering from trial-related problems or adverse events (AEs) may obtain medical treatment as compensation, and the trial is insured to compensate.

### Patients

Patients are recruited from one tertiary centre (Leeds Teaching Hospitals Trust) and two district centres (Harrogate District Foundation Trust and Bradford District Trust). Participants will have an implantable pacemaker for bradycardia for at least 12 months according to any indication in current accepted clinical guidelines^26^ and be able to provide written informed consent. Both atrial and ventricular pacing burdens will be documented. Participants will be excluded if they have an implantable cardioverter defibrillator or cardiac resynchronisation device, are less than 18 years old, pregnant, awaiting heart transplantation or have a severe comorbidity with life expectancy of <1 year. We will also exclude people with significant cognitive impairment and any already under the care of HF services.

### Randomisation and interventions

Potential participants will receive a thorough explanation of the process of the trial, be notified of appointments via post and associated travel costs will be available to maximise compliance. Potential participants will be asked to voluntarily provide written informed consent prior to randomisation in line with the Declaration of Helsinki 2002.

Consecutive pacemaker clinic attendees agreeing to participate will be enrolled and randomised centrally using a study-specific electronic system. Patients are randomised in a 1:1 ratio to (1) standard care pathway or (2) interventional pathway (figure 2). Usual care pathways follow National Institute for Health and Care Excellence (NICE) guidelines,^27^ and patients will undergo routine, usually annual, pacemaker follow-up. Interventional pathways consist of enhanced or optimised care predetermined by each recruiting site. The echocardiographically informed pathways will consist of either a primary care driven management plan based on the echocardiogram that will be forwarded to the primary care team (enhanced care, n=300) if recruited in one of the district centres or a comprehensive care package consisting of optimised programming and medical therapy co-ordinated by a regional HF service (optimised care, n=300) if recruited in the tertiary centre. This interventional package will include the RV pacing avoidance algorithm (figure 1) and in those with LVSD (LVEF <50%) medical therapy following the NICE guidelines for the management of CHF.^28^ In the presence of LVSD, patients recruited at the tertiary centre will be referred to an outpatient HF clinic (optimised care), and in the district centres an echocardiogram report will be sent to the patients’ general practitioner (enhanced care).

**Figure 2 F2:**
[figure not shown]
OPT-PACE study protocol.

### Blinding

Practitioners and participants in this trial cannot be blinded to allocation of treatment due to the nature of the intervention. By not participating in baseline assessments or medical and device optimisation and having no prior knowledge of participant allocation, the outcome assessor will remain blinded and thereby safe from detection bias.^29^ Unblinding of the assessors will only be permitted in certain circumstances, for example, when the information is demanded to ensure appropriate management of the participants (eg, serious AEs).

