### Outcome measures

The primary outcome measure is a combined endpoint of time from randomisation to date of first event of all-cause mortality or HF hospitalisation as assessed by the Endpoint Review Committee. The Endpoint Review Committee will ensure the quality of conduct and assess protocol deviations due to the low risk associated with intervention (echocardiography). They will monitor the safety of the trial and have unblinded access to efficacy data should it be required.

The main secondary outcome measure is the validation of a model to risk stratify people with a pacemaker for prevalent or future HF using simple clinical and pacing variables to predict the presence of LVSD at baseline and subsequently the combined outcome of HF hospitalisation and mortality at 1 year. Validation will be achieved by assessing against prespecified criteria, formed from the CIs of the initial pilot data analysis of the model.^9^

Other secondary outcome measures are to determine (1) the utility of BNP testing as a way to improve risk score for prevalent LVSD and future admissions, (2) hospitalisation rates and mortality across randomised arms, (3) utility of a diagnosis of cardiac dysfunction on achieving standard of care medications and doses and (4) quality of life as measured by the EuroQol 5-Dimension (EQ-5D) at baseline and 12-month postenrollment.

All AEs related to the interventions will be recorded and monitored until resolved. Medical personnel will decide if continued trial participation is feasible based on these reports, with the final decision made by the participant.

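### The exception that lets outcome assessors be unblinded for patient management serves no management purpose in this open-label trial and can weaken blinded classification of HF hospitalisation

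*Protocol article*

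**What the plan says.** The Blinding section of the protocol article makes three statements in sequence.

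- Care is open: "Practitioners and participants in this trial cannot be blinded to allocation of treatment due to the nature of the intervention".
- The assessor takes no part in baseline assessment or in medical or device optimisation, has no prior knowledge of allocation, and on that basis "the outcome assessor will remain blinded and thereby safe from detection bias".
- There is an exception: "Unblinding of the assessors will only be permitted in certain circumstances, for example, when the information is demanded to ensure appropriate management of the participants". Serious AEs are given in brackets as an example.

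The Outcome measures section defines the primary endpoint as "time from randomisation to date of first event of all-cause mortality or HF hospitalisation as assessed by the Endpoint Review Committee". Of that same committee it says: "They will monitor the safety of the trial and have unblinded access to efficacy data should it be required". On adverse events it says "All AEs related to the interventions will be recorded and monitored until resolved" and "Medical personnel will decide if continued trial participation is feasible based on these reports", with the participant having the final say.

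The article does not define a serious AE. It does not say whether endpoint events are exempt from the exception, or whether classification must be final before an assessor may be unblinded.

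**The concern.** Emergency unblinding normally exists so that the people treating a patient can learn what the patient was allocated to. In this trial they know from the start, and so does the patient. The people the exception would unblind are the assessors, who by the article's own account stay out of care. The reason given for the exception therefore does not fit the design.

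The example chosen also lies close to the primary endpoint. If a hospital admission counts as a serious AE, which is the usual meaning of the term but an assumption here, then an HF admission is both a possible occasion for unblinding and an event awaiting classification. Deciding whether an admission was for HF takes judgement, and blinded assessment is the only protection against detection bias that the article names. An assessor who knows the arm may, even without intent, classify borderline admissions differently between arms, and the hazard ratio for the primary endpoint would carry that difference.

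**Working it through.** The point rests on comparing statements, so the text comes first and the arithmetic only sets the scale.

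**1. Does anyone who manages the patient lack the allocation?** No. The Blinding section says practitioners and participants are unblinded.

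**2. Does the assessor manage the patient?** Not on the text. The Blinding section excludes the assessor from medical and device optimisation, and the Outcome measures section gives decisions after AE reports to medical personnel and the participant. From steps 1 and 2, disclosing the arm to an assessor serves no individual-management purpose.

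**3. Can the exception reach a patient whose event is unclassified?** Yes. The wording is open-ended (certain circumstances, with an example), has no carve-out for endpoint events and sets no condition on timing. An assessor unblinded around an admission stays unblinded when that admission is classified later.

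**4. Which events are exposed?** After a death no management remains for which the allocation could be requested, and all-cause death leaves little to misclassify. That leaves HF hospitalisation.

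**5. The plan's own event figure.** Inputs from the Sample size section: 15% versus 9% at 1 year, HR 0.58, two-sided 0.05, power 0.90, 146 events, N = 1200. Allocation is 1:1 (Randomisation and interventions section).

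- HR = ln(1 − 0.09) / ln(1 − 0.15) = 0.580, as stated.
- Schoenfeld: 4 × (1.960 + 1.282)² / (ln 0.58)² = 142 events.
- Freedman: (1.960 + 1.282)² × [(1 + 0.58) / (1 − 0.58)]² = 149 events.
- The stated 146 lies between the two, within 3% of each. It reproduces and is not in dispute.

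At the planned 12-month rates, 600 × 0.15 = 90 and 600 × 0.09 = 54, so about 144 primary events. This is an outer bound on the events the exception could touch, since it includes deaths. The split between deaths and HF hospitalisations is not given.

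**6. Illustration only, on assumptions that are not in the document.** Suppose no true effect, 15% events in both arms, 600 per arm, a share h of events that are HF hospitalisations, and a fraction m of intervention-arm HF hospitalisations wrongly rejected after unblinding.

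- Observed intervention rate: p = 0.15 × (1 − h × m).
- Spurious HR = ln(1 − p) / ln(0.85).
- Expected events: d = 600 × (0.15 + p).
- Shift of the log-rank statistic: √(d/4) × |ln HR|, from which the two-sided type I error follows.

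| h | m | Spurious HR | Type I error |
|---|---|---|---|
| 0.3 | 0.05 | 0.984 | 0.051 |
| 0.3 | 0.20 | 0.935 | 0.073 |
| 0.5 | 0.10 | 0.946 | 0.066 |
| 0.7 | 0.05 | 0.962 | 0.058 |
| 0.7 | 0.20 | 0.850 | 0.183 |

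The last row is a worst case within the range. Errors in the other direction are equally conceivable and would bias against the intervention.

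**The case against.** Six points can be made for the plan.

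- **The rule is restrictive and permissive, not automatic.** It says only in certain circumstances, and the condition is a demand for information needed for management. This stands. A reader might infer that every primary event sets off unblinding, so that all 146 planned events are affected. The document does not support that: a serious AE is an example of when a demand might arise, not a trigger.
- **If unblinding is never needed for management, the clause is inert.** This stands in part. A clause without a valid use may never be used. But the wording does not confine unblinding to the management example, and a permission without a valid purpose can still be exercised.
- **Timing.** The Data collection section records deaths and hospitalisations by digital follow-up at 12 months, so assessors may not be involved when a patient is admitted. This makes early unblinding less likely. It does not help where an assessor has been unblinded before the later classification.
- **The overlap depends on an undefined term.** The article does not define a serious AE, and the Outcome measures section limits recorded AEs to those related to the interventions. This stands as a limit on the overlap, although the Blinding section puts no such limit on its own example.
- **Assessor and committee may be different people.** The article does not equate them. However, it has the Endpoint Review Committee assess the primary endpoint and also monitor safety with possible unblinded access. The two sections therefore need reconciling on either reading. The committee's role may be a reason for someone to review unblinded data, but it is not the individual-management reason given under Blinding.
- **This is a condensed article.** Logging and adjudication procedures may well be in the full protocol or a committee charter, and their absence here is no finding. The point concerns a rule the article does state, whose reason conflicts with the sentences before it.

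**Conclusion.** The concern holds in a limited form. The exception allows assessors to be unblinded for a purpose that the open-label design already meets by other means. It can be invoked while an admission still awaits classification as HF hospitalisation, so the claim of safety from detection bias is stronger than the stated rule supports.

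The exposure is essentially HF hospitalisation. Its size is unknown: the article gives neither the mix of event types nor how often the exception would be used. The spurious hazard ratios of 0.98 to 0.85, and type I errors of about 0.051 to 0.18, show what assumed misclassification would do and are not estimates for this trial. The overlap itself assumes that hospital admissions count as serious AEs. The 146 events and the sample size are unaffected.

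**What to change.** Replace the exception in the Blinding section with a rule such as: *Assessors of the primary endpoint are not unblinded to a patient's allocation before the classification of that patient's events is final. Any safety need for the allocation is met by the treating team, who already know it.*

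Then reconcile this with the Outcome measures section, which lets the committee that assesses the primary endpoint also monitor safety and see unblinded efficacy data. One way is to keep the adjudicating members blinded and give any unblinded safety review to separate people.

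The cost is one replaced rule and a matching clarification of the committee's role; separate safety reviewers, if chosen, would have to be named. Nothing is withheld from treating staff or participants, and no sample-size or analysis figure changes.

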### Outcome measures

The primary outcome measure is a combined endpoint of time from randomisation to date of first event of all-cause mortality or HF hospitalisation as assessed by the Endpoint Review Committee. The Endpoint Review Committee will ensure the quality of conduct and assess protocol deviations due to the low risk associated with intervention (echocardiography). They will monitor the safety of the trial and have unblinded access to efficacy data should it be required.

The main secondary outcome measure is the validation of a model to risk stratify people with a pacemaker for prevalent or future HF using simple clinical and pacing variables to predict the presence of LVSD at baseline and subsequently the combined outcome of HF hospitalisation and mortality at 1 year. Validation will be achieved by assessing against prespecified criteria, formed from the CIs of the initial pilot data analysis of the model.^9^

Other secondary outcome measures are to determine (1) the utility of BNP testing as a way to improve risk score for prevalent LVSD and future admissions, (2) hospitalisation rates and mortality across randomised arms, (3) utility of a diagnosis of cardiac dysfunction on achieving standard of care medications and doses and (4) quality of life as measured by the EuroQol 5-Dimension (EQ-5D) at baseline and 12-month postenrollment.

All AEs related to the interventions will be recorded and monitored until resolved. Medical personnel will decide if continued trial participation is feasible based on these reports, with the final decision made by the participant.

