### Data collection

A clinical research co-ordinator (CRC) will collect information on demographic characteristics such as gender, age, vital signs, height and weight and medication history. The patients’ medical history will be taken along with pacemaker data (implant date, implanted device, programmed pacemaker mode, BR and cumulative pacing percentages), and blood draw will be obtained. Biological specimens will be analysed and stored in the onsite research pathology laboratory. Patients randomised to intervention will undergo a baseline transthoracic echocardiogram, which will be assessed by the CRC. All data will be stored anonymously and will be locked once complete.

To ensure protocol adherence, a single research team will undertake all study-specific activity and be regularly monitored.

Digital follow-up will occur at 12-month postrecruitment to record mortality and hospitalisation data and changes to medical therapy. Patient data regarding cardiac transplatation or device upgrade will be recorded and subsequently reported.

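### The committee that adjudicates heart failure hospitalisation may also see unblinded efficacy data, so the masking behind the detection-bias claim is not secured

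*Protocol article*

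**What the plan says.** All of this is in the protocol article.

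- **Outcome measures, endpoint.** The primary outcome is "time from randomisation to date of first event of all-cause mortality or HF hospitalisation as assessed by the Endpoint Review Committee". The committee is therefore the outcome assessor.
- **Outcome measures, other duties.** The same committee looks after quality of conduct and reviews protocol deviations, an arrangement explained by the low risk of the intervention. The next sentence reads: "They will monitor the safety of the trial and have unblinded access to efficacy data should it be required".
- **Blinding, treatment side.** "Practitioners and participants in this trial cannot be blinded to allocation of treatment due to the nature of the intervention".
- **Blinding, assessor side.** Because the assessor takes no part in baseline assessment or optimisation and has no prior knowledge of allocation, "the outcome assessor will remain blinded and thereby safe from detection bias".
- **Blinding, exception.** "Unblinding of the assessors will only be permitted in certain circumstances, for example, when the information is demanded to ensure appropriate management of the participants"; serious adverse events are the example given.
- **Methods and analysis, opening paragraph.** An independent trial steering committee is mentioned only as one of the bodies that approved the design and protocol.

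**The concern.** One committee holds two kinds of duty that pull against each other. Adjudication needs people who do not know the arm. Review of deviations, safety and efficacy can require or reveal it. The Blinding section claims freedom from detection bias without qualification, and Outcome measures gives the assessor a route to the information that the claim says it lacks.

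This matters because the trial is open and the intervention is diagnostic. It labels some patients as having left ventricular systolic dysfunction, and at the tertiary centre those patients are referred to an HF clinic. Whether an admission is attributed to HF is a judgement that knowledge of such a label could influence in either direction. All-cause death is not open to that influence. The exposure is therefore confined to the HF-hospitalisation component, for which masked adjudication is the only safeguard the article states.

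**Working it through.** **Step 1: the text.** The point rests on comparing two sections, not on a figure.

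| Question | Blinding | Outcome measures |
|---|---|---|
| Who assesses the endpoint? | The outcome assessor | The Endpoint Review Committee |
| Does the assessor know the arm? | No; stays blinded | May access unblinded efficacy data if required |
| When may masking be lifted? | Certain circumstances; example is managing participants with serious adverse events | When required; no purpose or limit given |
| Other duties? | None in baseline or optimisation work | Conduct, protocol deviations, safety |

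The exception in Blinding is open-ended, but its example concerns the care of individual participants. Looking at efficacy data is a different purpose, so the exception does not clearly cover it.

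Deviation review is a second route. Under Randomisation and interventions and Data collection, only the intervention arm has the study echocardiogram and the echo-informed pathway. A deviation from either would identify the arm.

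The reason given for the arrangement is low intervention risk. That can justify light safety oversight. It does not bear on detection bias, which does not depend on how risky the intervention is.

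**Step 2: does it touch the design figures?** Sample size states 15% against 9%, hazard ratio (HR) 0.58, two-sided 0.05, power 0.90 and 146 events.

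- HR = ln(0.91)/ln(0.85) = 0.580, as stated.
- Required events are 142 (Schoenfeld) and 149 (Freedman). The stated 146 lies between them.

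The point changes neither the event target nor the number of participants.

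**Step 3: illustrative range.** The article does not give the HF share of first events or any misclassification rate, so both are assumed. Let *s* be the HF share and *r* the proportion of HF events removed in the intervention arm only, with a true HR of 1.00. Then:

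- reported HR = 1 − *s* × *r*
- standard error of log HR ≈ 2/√146 = 0.166, holding events at the planned 146
- *z* = |ln HR|/0.166
- false-positive rate = Φ(*z* − 1.96) + Φ(−*z* − 1.96)

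| *s* | *r* | Reported HR | Inverse, if the control arm is affected | False-positive rate (nominal 5%) |
|---|---|---|---|---|
| 0.25 | 0.15 | 1 − 0.0375 = 0.96 | 1.04 | 5.6% |
| 0.50 | 0.15 | 1 − 0.075 = 0.925 | 1.08 | 7.6% |
| 0.75 | 0.30 | 1 − 0.225 = 0.775 | 1.29 | about 34% |

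In the middle row ln(0.925) = −0.078. That is under half a standard error (0.078/0.166 = 0.47) and about 14% of the design effect (0.078/0.545, with ln 0.58 = −0.545). Each row overstates the shift for its inputs, because a patient whose HF admission is declassified but who later dies in follow-up still contributes an event.

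**The case against.** **Neither statement is absolute.** Blinding allows exceptions, and access to efficacy data applies only if required. Such data might also be arm-level summaries that reveal no individual's allocation. This stands in part. A reader might infer that adjudication will be unblinded, or that an HF difference could not be told apart from labelling. The documents do not support that; they show masking that is not secured.

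**An article condenses a longer document.** A charter may separate the roles, and packet content and redaction belong there. Their absence is indeed no finding. But the article does more than omit a firewall: it assigns all the duties to one committee and gives a reason. That conflict lies in the published text.

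**Two further inferences are tempting and do not hold.** First, Data collection says that "a single research team will undertake all study-specific activity and be regularly monitored", which might be read as placing adjudicators among those who know the allocation. The committee is named separately and nothing says that the team sits on it, so there is no contradiction. Second, a reader might infer that the clinical records necessarily unblind the adjudicators. The article does not say what the committee is shown, so this is only a reason to specify redaction.

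**The size is invented.** The inputs are assumed, and moderate values move the HR little against the design effect. This stands. The table is a range under stated assumptions, not an estimate of bias in this trial.

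**Conclusion.** The concern holds in a limited form. Outcome measures gives the assessor of the primary endpoint duties and conditional data access that do not fit the flat claim in Blinding, and the stated exception does not clearly bridge the gap. In an open-label trial this leaves the judgement-based component of the composite without a secured safeguard.

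The limits are that access is conditional, deaths are unaffected, the direction of any bias is unknown, and the planned sample size and event count stand. No size can be derived from the documents. Under the assumptions above it runs from negligible (HR 0.96) to serious (HR 0.78), depending on the HF share and the degree of one-sided reclassification. The conclusion rests on the article as written; a charter that already separates the roles would reduce it to a wording correction.

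**What to change.** Reconcile Blinding with Outcome measures:

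1. **Adjudicators.** Those who classify HF hospitalisation do only that, masked to arm, with the study echocardiogram, reprogramming and study HF referral redacted. They have no access to efficacy data by arm.
2. **Other duties.** Give protocol deviations, safety and any unblinded data to people who do not adjudicate. These could be non-adjudicating members of the committee, or the existing independent steering committee. The article gives the latter only an approval role, so its remit would need extending and its access to comparative data defining.
3. **If this is not done,** withdraw the statement that assessment is safe from detection bias and report the limitation.
4. **Sensitivity analysis.** Add death or any unplanned hospitalisation, using the 12-month digital follow-up already planned. It does not depend on attributing an admission to HF. It does not remove any effect of open treatment on the decision to admit. No separate death-alone analysis need be added, since mortality by arm is already a secondary outcome.

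The cost is charter and protocol wording, redaction work and one extra analysis. No new committee is needed.
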